### Statistical analysis

Descriptive data will be presented using descriptive statistics. The participant’s barefoot questionnaire and the PAQ outcomes will be compared to all attending children in 2 primary (1 rural, 1 urban) and 2 secondary schools to assess external validity. The outcome measures will be evaluated for normality using Shapiro-Wilkins and visually using P-P plots, if possible, non-normal distributed data will be adjusted. Mixed Models linear regression will be used to assess if the foot mechanical and motor performance outcomes differ between the barefoot and the shod participants (fixed factors). Furthermore, we will test differences due to being barefoot or shod change by age by adding an interaction of age*group to the linear regression. Differences in foot strike pattern during jogging and sprinting between barefoot and shod participants will be assessed using ordinal regression. The school of a participant will be added to the model as a random effect in order to adjust for possible differences between the schools and their geographical location. Furthermore, Gender, BMI, PAQ-Score, ethnicity and inside/outside testing will be tested for confounding in all models (regression coefficient changes >10 %). We hypothesize that older boys could have higher arches (lower dAI) [37] and perform better on motor performance tasks, while girls’ feet will show a higher pliability. BMI increases the dAI and possibly decreases motor performance [38, 39]. A higher level of physical activity (higher PAQ score) is probably related to better motor performance. And lastly, Caucasians could have higher arches (lower dAI) [40].

We anticipate that gender might modify the effect of being barefoot or shod on the outcome measures and therefore gender will additionally tested as an effect modifier (interaction between outcome and gender *p* < 0.1). In all cases, a significance level of 5 % is pre-stipulated.

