**Methods:**

This study has a cross-sectional, binational design and is part of the “Barefoot Locomotion for Individual Foot- and health Enhancement (Barefoot LIFE)” project. Two large cohorts (n_(total)_ = 520) of healthy children and adolescents between 6 and 18 years of age will be included respectively in Germany and South Africa. A barefoot questionnaire will be used to determine habitually barefoot individuals. The testing will be school-based and include foot mechanical (static arch height index, dynamic arch index, foot pliability) and motor performance (coordination, speed, leg power) outcomes. Gender, BMI and level of physical activity will be considered for confounding.

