### Sample size

Although we did not opt to distinguish primary or secondary outcome measures, the dAI was used to enable a sample size calculation. Muller et al. [36] has shown that the average dynamic arch index (μ: 0,19) and the accompanying standard deviation (SD: 0065) are stable between the ages of 6 and 13. The minimal important difference was set at 20 % of the average (0.19; i.e., 0.038). With a two-sided significance level of 0.05, and assuming a power of 0.8, a minimum of 16 participants per age group, per country, had to be included for this study. Due to the diversity of the study, additional power calculations have been performed. Based on the arch height ratio derived from Waseda et al. [22] the sample size for arch height ratio (navicular height*100/foot length) should be *n* = 12 per age group (μ = 15,0; SD = 2,6). Furthermore, based on a preliminary study on children, the sample size based on the standing long jump should be *n* = 18 (μ = 152,9; SD = 31,5), for lateral jumping *n* = 22 (μ = 38; SD = 9,2) and for 20 m sprint *n* = 12 (μ = 3,81; SD = 0,64). Therefore, our *n* = 20 per group seems to be sufficient. In order to allow for these differences and other unknown variances within the other variables we choose to increase the number from 16 to 20 participants per age group, per country.

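### Normality is checked on the outcome measures, not on the mixed-model residuals, and it triggers an undefined adjustment that may needlessly change the scale on which the age-by-group interaction is tested

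*Protocol article*

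**What the plan says.** All of the rule is in the protocol article, Statistical analysis. The distributional check is: "The outcome measures will be evaluated for normality using Shapiro-Wilkins and visually using P-P plots, if possible, non-normal distributed data will be adjusted". The object of the check is the outcome variable, and the response to failure is to change the data.

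The next sentence gives the model: "Mixed Models linear regression will be used to assess if the foot mechanical and motor performance outcomes differ between the barefoot and the shod participants". The section adds a school effect ("The school of a participant will be added to the model as a random effect") and examines age-dependence by "adding an interaction of age*group to the linear regression". Age-dependence is one of the aims in the Background and is repeated in the Discussion.

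The section does not say whether the check is run on all children together, by group, or by age. It does not define the adjustment, and it mentions no check of residuals.

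On design, the abstract describes "Two large cohorts (n_(total)_ = 520) of healthy children and adolescents between 6 and 18 years of age", and the Sample size section fixes equal numbers per age: "we choose to increase the number from 16 to 20 participants per age group, per country".

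**The concern.** A linear mixed model makes its distributional assumption about what remains after the fixed effects have been removed, and about the school effects. An outcome can be far from normal overall and still satisfy the model exactly. This happens when a strong predictor is spread evenly over a wide range, as age is in this design.

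The check therefore looks at the wrong quantity, and a change of the data depends on it. Interactions depend on scale. A group difference that is constant over age in centimetres is not constant in log centimetres. If an outcome is transformed because its overall distribution is flat or skewed through age alone, the answer on age-dependence may change for a reason unrelated to model fit. The planned test of gender as an effect modifier faces the same risk. Results would also leave the units in which the minimal important difference is set (0.038 for dAI, Sample size section).

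**Working it through.** **Inputs from the article.** Ages 6 to 18 make 13 one-year groups, with 20 children per age group per country. 13 × 20 × 2 = 520, which reproduces the stated total and gives 40 children per age. The long-jump mean is 152.9 (Sample size section). The dAI mean and SD are described there as stable from 6 to 13 years.

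**Inputs assumed.** The article gives no age trend for any motor outcome. I let age explain 30 to 80% of the variance. *Adjusted* is read as a nonlinear transformation, and the test as pooled over ages at the 5% level.

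**Step 1: why flat recruitment matters.** Let the outcome be slope × age + normal error with SD 1.
- The variance of 13 equally frequent ages is (13² − 1)/12 = 14.
- The share of variance due to age is R² = 14b²/(14b² + 1), with b the slope in residual SD per year. So b = 0.2, 0.3, 0.4 and 0.5 give R² = 0.36, 0.56, 0.69 and 0.78.
- The excess kurtosis of 13 equally frequent values is −6(13² + 1)/[5(13² − 1)] = −1.21. For the outcome it is −1.21 × R⁴, which is −0.30 at R² = 0.5 and −0.78 at R² = 0.8.

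The outcome is flat-topped although the errors are exactly normal.

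**Step 2: how often Shapiro-Wilk rejects.** Simulated samples of 520 children, 40 per age, with exactly normal errors:

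| Variance explained by age (assumed) | Test on outcome | Test on residuals |
|---|---|---|
| 30% | 4% | about 5% |
| 50% | 17% | about 5% |
| 60% | 46% | about 5% |
| 70% | 86% | about 5% |
| 80% | 100% | about 5% |

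A separate simulation, indexed by slope and including a group shift of 0.038/0.065 = 0.58 SD, agrees. The outcome test rejects in 5, 5, 6, 22, 75 and 99% of samples at 0, 0.1, 0.2, 0.3, 0.4 and 0.5 SD per year. The residual test rejects in 5 to 6% throughout. With the trend levelling off at age 14, the outcome test gives 5, 5, 7, 26, 79 and 100%. No school effect was simulated there.

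**Step 3: other readings of who is pooled.**
- Tested in each group separately (n = 260), at least one group fails in 16, 34, 69 and 98% of runs at shares of 50, 60, 70 and 80%.
- Tested in each of the 26 age-by-country cells (n = 20), at least one cell fails by chance with probability 1 − 0.95²⁶ = 0.74 (simulated: 73%).

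**Step 4: effect of a transformation on the interaction.** Take a constant long-jump difference of 20% of 152.9 = 30.58, so there is no age-by-group interaction on the original scale. After a log transformation:
- if means run from 120 to 185 (assumed): ln(150.58/120) = 0.227 at age 6 and ln(215.58/185) = 0.153 at age 18;
- if means run from 100 to 205 (assumed): ln(130.58/100) = 0.267 and ln(235.58/205) = 0.139.

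An interaction appears that was absent before.

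**The case against.** Four points can be made for the plan.

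1. *The text does not say that the test is pooled or that data are transformed.* This stands; both are readings. A reader might infer that the plan commits to pooled testing of raw outcomes and that outcomes will be transformed needlessly. The article supports neither as a statement of fact. The qualifier that adjustment happens only where possible, and the P-P plots beside the test, leave the analyst discretion. Testing by group or by cell does not rescue the rule, however (Step 3).

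2. *A log does not cure a flat distribution.* This stands for linear trends. Using the long-jump mean and SD with age shares of 50 to 80%, a log restored normality in none of the failing samples, and a square root in 13, 3, 1 and 0%. An analyst might then conclude that adjustment is not possible and keep the original scale. It does not hold for curved trends. With an assumed curvilinear age trend in sprint time, the outcome test failed in 86 to 100% of samples, and a log restored normality in 72% of those at an age share of 50% and in 19% at 70%. A needless transformation is therefore possible, but not certain.

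3. *The age trends are undocumented.* This stands. For dAI, the stated stability at ages 6 to 13 means that no needless adjustment is expected over that range. Foot strike pattern goes to ordinal regression and is outside the point.

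4. *Model diagnostics belong in an analysis plan, which is not shown.* The absence of a residual check alone would be no finding. But the article states a rule, and the rule is applied to the wrong quantity.

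**Conclusion.** The point holds in conditional form. The check is applied to the outcomes, whereas the model's assumption concerns residuals and school effects, and the action tied to the check is undefined.

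For outcomes with a strong age trend, most plausibly the motor tests, the pooled check would reject in about 17 to 100% of samples at assumed age shares of 50 to 80%, although the model fits. At a share of 30% or less there is no excess over 5%. Whether a transformation follows depends on what *adjusted* means, on the shape of the trend and on the analyst's judgement. If one follows, the age-by-group interaction is tested on another scale and may appear or vanish for that reason.

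The documents do not support the stronger statement that outcomes in general will be transformed needlessly, and they do not support the point for dAI at ages 6 to 13. The sample size does not depend on this rule. The wording should be changed before analysis, because the change is small and one of the study's stated aims is exposed.

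**What to change.** Replace the sentence on normality with wording to this effect: *Residuals and estimated school effects of each fitted linear mixed model will be inspected with Q-Q and residual plots. The original scale is the main analysis. A transformation will be considered only if residuals are clearly non-normal; it will be named, and its result reported beside the original-scale result.* Drop the Shapiro-Wilk test on the outcomes as a trigger.

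Transformation is not banned, since an outcome with multiplicative effects may call for it. Confidence intervals from a bootstrap that resamples schools are an option if residuals are poor, but only with enough schools. The article gives contact blocks of five primary and five secondary schools, not a final number.

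The cost is one or two sentences and slightly more analysis work. Recruitment, measurements and sample size are unaffected.

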**Discussion:**

The strength of this study is the comparison of two large cohorts with different footwear habits to determine long-term effects of being habitually barefoot on foot mechanics and motor performance.

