### Study design

This is a binational multicenter, cross-sectional observational study looking at differences of foot mechanics and motor performance between habitually barefoot and habitually shod children and adolescents aged 6–18 years. Ethical approval has been obtained from the ethics committee of the medical association Hamburg (protocol number PV4971) and Stellenbosch University ethics committee (protocol number HS1153/2014). The regional separation of the recruitment is due to the obligation of footwear use in most German educational institution while in South Africa the habit of being barefoot prevails.

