### Testing procedure

Methodological planning stipulates all anthropometrical, foot and motor performance measurements to be performed during a physical education lesson. Prior to the testing, a physical activity questionnaire for children/adolescent (PAQ-C and PAQ-A [25, 26]) and a barefoot questionnaire will be distributed by the teachers and collected by the study staff on the testing day and briefly checked for completeness. All children bringing the signed consent form and voluntarily want to participate will be gathered and all relevant information for the testing will be given by the principal investigator. After a short warm up period (jogging for < 5 min), participants will be randomly allocated to the seven testing stations:AnthropemetryFoot caliperPressure plate20 m sprintingLateral jumpingStanding long jumpBackwards balancing

After their first testing station, a participant will be transferred to the next vacant station without a fixed order. Testing station 1–3 will be completed only barefoot, while testing stations 4–7 will be performed in barefoot and shod conditions. The order of the condition is randomized a priori on the registration sheet which is distributed to the participants on the testing day. A flowchart displaying the participant flow through the study is shown in Fig. 1.

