### Motor performance

The criterion for the selection of these motor performance tests is related to the expected effects of habitual barefoot locomotion on lower limb gross motor skills, even though the evidence for the effects of habitual barefoot locomotion on motor performance is unclear [[name], Heidt C, [name], [name], [name]. Long-term effects of habitual barefoot running and walking: a systematic review. Manuscript submitted for publication].

The tests used to assess motor performance have been used in other studies, and have been shown to be valid and reliable [34, 35]. Even though all tests have been extensively practiced by the main researchers, the researchers from both countries combined and separate, it is imaginable that regional characteristics and the use of different examiners as well as test equipment will influence the results. An example is that the sprinting will be mostly done outdoors in South Africa due to a lack of indoor sport facilities at some schools which might be influential on the 10 m and 20 m sprint time. By adding a variable for outdoor/indoor running we will test if it acts as a confounder and adjust the outcome accordingly. Another difference between testing in Germany and South Africa is the speed gates used. Mobile magnetic timing gates will be used in Germany while in South Africa single beam speed gates will be used [53]. The latter is less accurate, however, the measurement error is still small (0.01 s) [54]. Therefore, no adjustments will be made when comparing the two countries.

Another limitation could be that measuring the distance during the standing long jump is done visually by one of the researchers by placing a right-angled rod at the place the heel landed. By using the average of three tries the influence of possible random measurement errors would decrease. Nonetheless, to provide comparability to other studies [34, 35], we will use the best of three tries. When using the backward balance test, a possible limitation would be a ceiling effect since there is a maximum of 8 steps per beam. However, by adding the steps for all the beams and the likelihood of not reaching the maximum 8 steps on the 4.5 and 3 cm beam, it is unlikely that a ceiling effect will occur. The score (i.e., the sum of the trials) will be treated as a continues variable during data analysis.

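### A random school effect does not adjust for geographical location, so Germany v South Africa differences left after confounder adjustment pass wholly or partly into the barefoot coefficient

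*Protocol article*

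**What the plan says.** The Abstract (Methods) describes "Two large cohorts (n_(total)_ = 520") that "will be included respectively in Germany and South Africa". Study design explains the split: recruitment is separated by region "due to the obligation of footwear use in most German educational institution while in South Africa the habit of being barefoot prevails". The Sample size section sets 20 participants per age group per country; it does not set numbers by barefoot status. Status itself comes from a questionnaire with a stated rule (Barefoot questionnaire).

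Under Statistical analysis, a linear mixed model compares barefoot with shod participants, with an age-by-group interaction added. School enters as a random effect "in order to adjust for possible differences between the schools and their geographical location". Gender, BMI, PAQ score, ethnicity and inside/outside testing are screened as confounders by a change of more than 10% in the coefficient. Country is not on that list and not in the model.

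The Discussion (Motor performance) allows, as a possibility, that "regional characteristics and the use of different examiners as well as test equipment will influence the results". It also says that the two countries use different timing gates and that no adjustment will be made for this. The Abstract (Discussion) still presents the comparison of cohorts as a way "to determine long-term effects of being habitually barefoot on foot mechanics and motor performance".

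**The concern.** A random school intercept allows for the fact that children in one school resemble each other. It assumes that school effects are unrelated to the fixed effects. Here they are related: South African schools supply most of the barefoot children and German schools most of the shod ones. Anything else that differs systematically between the two sets of schools then lines up with the exposure, and the model has no other term to put it in.

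The coefficient at risk is the main one for all the foot mechanics and motor performance outcomes. A larger sample would not help, because it would only make the same mixture more precise. The Background criticises earlier studies for comparing participants from different continents and backgrounds; the planned analysis leaves this study open to the same criticism while saying that location has been adjusted for.

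**Working it through.** **The plan's own figure.** 13 one-year age groups (6 to 18) × 20 children × 2 countries = 520, which matches the Abstract. The comparison is built by country, with 260 children in each.

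**Why the random effect does not adjust.** The planned model is y = β0 + β1·(barefoot) + u(school) + e, with u centred on zero and independent of barefoot status. Suppose the true barefoot effect is 0 and all South African schools are shifted by δ. If barefoot status and country coincide, β1 estimates 0 + δ. If they overlap only in part, β1 is a weighted average of the within-school contrast, which is free of δ, and the between-school contrast, which carries it. Part of δ then remains.

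**How much of the shift enters.** Inputs from the Sample size section: δ = 0.038 (the plan's minimal important difference for the dynamic arch index) and SD = 0.065 (printed 0065). Assumptions not in the document: 10 schools per country, 26 children per school, school SD 0.015 (ICC = 0.015²/0.065² ≈ 0.05), and the barefoot shares. There were 200 simulated studies per row, with a true barefoot effect of 0. Share entering = estimate/0.038.

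| Barefoot share, South Africa/Germany | Correlation with country | Planned model: estimate | Share of δ entering | With country fixed: estimate (SE) | Rejection with country fixed |
|---|---|---|---|---|---|
| 100%/0% | 1.00 | 0.0383 | about 100% | not estimable | n/a |
| 95%/2% | 0.93 | 0.0284 | 75% | −0.0003 (0.0156) | 6.5% |
| 90%/0% | 0.90 | 0.0262 | 69% | −0.0017 (0.0133) | 5.0% |
| 80%/5% | 0.76 | 0.0137 | 36% | 0.0007 (0.0088) | 3.5% |

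Wherever the country term can be estimated, it removes the bias, and rejection returns to about 5%.

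**False positives for smaller shifts.** The size of the residual country shift is unknown, so a range is needed. With full overlap, ICC 0.05 and total SD 1, SE = √(2 × (0.05 + 0.95/26)/10) = 0.132. The two-sided 5% rejection rate is approximately Φ(δ/SE − 1.96) + Φ(−δ/SE − 1.96):

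- δ = 0.1 SD: 0.1/0.132 = 0.76, giving about 12%
- δ = 0.2 SD: 0.2/0.132 = 1.52, giving about 33%
- δ = 0.3 SD: 0.3/0.132 = 2.28, giving about 63%

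A simulation of 1,000 studies on the same assumptions gives 12%, 34% and 64%. If 70% of South African children are barefoot, it gives 8%, 12% and 24%.

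**Precision of a within-country contrast.** Detectable difference at 80% power = 2.80 × √(1/n1 + 1/n2), using the 260 South African children pooled over ages and ignoring clustering:

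- 70% barefoot (182 v 78): 2.80 × 0.135 = 0.38 SD
- 90% barefoot (234 v 26): 2.80 × 0.207 = 0.58 SD
- 95% barefoot (247 v 13): 2.80 × 0.285 = 0.80 SD

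The standard errors in the table give similar values: 2.80 × 0.0133/0.065 = 0.57 SD at 90%/0%, and 2.80 × 0.0156/0.065 = 0.67 SD at 95%/2%. In a single age group of 20 split 14 v 6, the figure is 2.80 × √(1/14 + 1/6) = 1.37 SD.

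**The case against.** The case for the plan has several sound parts.

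- Barefoot status is set by questionnaire, not by country, and no passage gives the share in either country. A reader might infer that the coefficient is simply a country difference under another name. The documents do not support that: it would be true only at complete overlap, and under partial overlap only part of the shift enters.
- Some country differences are handled. Ethnicity, inside/outside testing, BMI and PAQ score are screened as confounders. South African recruitment aims at ethnic backgrounds similar to the German ones. Examiner differences are reduced by joint training, the attendance of a principal investigator in the first weeks in South Africa, and inter-rater testing (Outcomes). The stated timing-gate error of 0.01 s is small against the sprint SD of 0.64 s (0.01/0.64 ≈ 0.016 SD) and concerns sprinting only.
- The two-country design is disclosed, and regional influence is raised as a possibility, not admitted as a fact.
- A reader might infer that a clean within-country comparison is already being collected, because "All children bringing the signed consent form and voluntarily want to participate will be gathered". That sentence covers testing. The eligibility criteria do not exclude non-barefoot South African pupils, but nothing says how many there will be or that they will be analysed as shod. Such a contrast could still be confounded by ethnicity, rural or urban setting and school type.
- It would also be wrong to set the pooled 0.38 SD against the plan's 0.038/0.065 = 0.585 SD and conclude that power is ample. The latter sizes one age group; the former pools 13 and assumes 70% barefoot.

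These points limit the size of the problem and the reach of the remedy. They do not rescue the statement about the school effect. Any country difference outside the tested confounders remains unadjusted.

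**Conclusion.** The statement that the random school effect adjusts for geographical location is wrong as written. Barefoot status is largely aligned with country by design, schools are nested in country, and country appears nowhere in the analysis. Residual country differences enter the barefoot coefficient in full at complete overlap, and to about 36% to 75% at the partial overlaps examined.

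The structural point needs no assumed figure. The sizes do: the number of schools, the ICC, the barefoot shares and the residual shift are all assumptions. The false-positive rate at full overlap runs from about 12% to 64% over shifts of 0.1 to 0.3 SD, and the document gives no basis for choosing within that range. It also does not establish that such a shift exists, only that the planned model could not separate it from a barefoot effect. Reading the coefficient as a long-term effect of being habitually barefoot is therefore not supported by the analysis as planned.

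**What to change.** 1. Delete the claim that the school random effect adjusts for geographical location. Keep the effect for clustering.
2. Report the share of children classified as barefoot in each country, overall and by age.
3. Where questionnaire status varies within country, add country as a fixed effect and report the within-country contrast (mainly barefoot v non-barefoot South African children) beside the pooled one for each outcome.
4. Where overlap is too small or absent, so that country is imprecise or inestimable beside group, word the conclusion as a difference between South African barefoot and German shod children, not as an effect of being habitually barefoot.

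This needs one model term, extra table rows and conditional wording, and no new measurements. The cost is precision, and it depends on a share that is not yet known. Pooled over ages, the detectable difference is about 0.38 SD if 70% of South African children are barefoot, about 0.57 SD at 90% and 0.7 to 0.8 SD at 95%. Single age groups are much less precise, so the age-by-group question suffers most. The within-country contrast should be presented with its own remaining confounding by ethnicity, setting and school type.
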